### Objectives

Our primary objective will be focused on assessing feasibility. Feasibility will be assessed by measuring the recruitment rate, retention rate, and completion rate at 3 months following surgical repair as well as the recruitment time.

Our secondary outcomes will include a) macular hole closure rate at 3 months following surgery; two independent readers, masked to treatment allocation, will independently grade the outcome in each instance as closed, or open. Outcomes classified as open will be further divided into open and flat (without a cuff of subretinal fluid), or open and elevated (with a cuff of subretinal fluid). b) best-recorded visual acuity at 3 months post-surgery, c) compliance with FDP as assessed utilizing self-administered questionnaires four times per day during the duration of FDP, d) patient self-administered vision-specific validated quality of life measure, the 25-item National Eye Institute Visual Function Questionnaire (NEI VFQ-25) and a validated quality of life measure, the Quality of Life Scale (QOLS), and e) complication rates (endophthalmitis, retinal detachment, vitreous hemorrhage) as assessed by a masked physician.

The interpretation of findings will be: a) the full-scale trial is feasible with no changes to the protocol; b) the full-scale trial is feasible with small changes to the protocol; c) the full-scale trial is infeasible. The study will be considered feasible if the retention and completion rates are > 80% of randomized patients. The study will be considered feasible with small changes if either the retention or completion rate is <80% of randomized patients and the study will be considered infeasible if the completion and retention rates are <80% of randomized patients.

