### Eligibility criteria

All consecutive treatment naïve patients with an idiopathic FTMH with a symptom duration of less than 6 months who agree to participate will be included in this investigation. Patients with macular hole minimum diameter >1000 μm, a history of high myopia (> -6), traumatic macular hole, amblyopia, retinal vein occlusion, inflammatory eye diseases, or who were found to have a retinal tear during either the pre-operative assessment or intraoperatively will be excluded.

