### Randomization and masking

Patients will be randomized 1:1 to the 3-day FDP or 7-day FDP groups utilizing permuted block randomization with blocks of 4, 6, and 8. Sequence generation will be performed in R (version 4.3.1, Vienna, Austria) by a research team member with experience generating lists for RCTs. The list will subsequently be uploaded to the online secure research platform Research Electronic Data Capture (REDCap) and allocation concealment will be maintained utilizing REDCap. Randomization will be performed immediately following completion of the surgical case and the surgeon will be immediately made aware of the patient’s allocation. At this point, the surgeon will inform the patient in the recovery room regarding their treatment allocation. Allocation concealment will be maintained utilizing REDCap. The randomization list will be made available to the remaining study team following the completion of the study.

All staff performing VA assessments and obtaining OCT images will be masked to treatment allocation. OCT grading of FTMH closure will be performed by two masked readers and disagreements will be resolved by a third masked reader. The participants themselves and the clinical teams managing their care will be unmasked.

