### Statistical methods and data analysis

Regarding the primary outcomes, the recruitment rate will be calculated as the number of patients randomized / the number of eligible patients screened. The retention rate will be defined as the number of patients who complete the follow-up measures at 3 months / the number of enrolled participants. Completion rates for data collection will be defined as the number of complete datasets for each of the outcome measures at 3 months / number of participants enrolled in the study. The recruitment time will be defined as the time taken in days to recruit 40 participants from the start of the enrollment period.

For the secondary outcomes, analyses will be performed on an intention-to-treat basis. Continuous variables will be expressed as means (± standard deviation) and categorical variables will be expressed as percentages. Continuous variables will be compared utilizing the student’s t-test or Mann-Whitney U test based on normality. Categorial variables will be compared utilizing the Chi-Squared Test. Fisher’s Exact Tests were performed for expected values less than five. A p-value of <0.05 will be considered statistically significant. All estimations will be reported with 95% confidence intervals. All analyses will be performed using R (version 4.3.1; R Foundation, Vienna, Austria).

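### The three-tier feasibility rule uses two denominators (randomized and enrolled) and gives no verdict when a rate is exactly 80%, so the primary conclusion is not fixed as written

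*Protocol article*

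**What the plan says.** The Objectives section of the protocol article gives the verdict rule in three parts, each on randomized patients:

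- Top tier: "The study will be considered feasible if the retention and completion rates are > 80% of randomized patients".
- Middle tier: "feasible with small changes if either the retention or completion rate is <80% of randomized patients".
- Bottom tier: "the study will be considered infeasible if the completion and retention rates are <80% of randomized patients".

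The Statistical methods and data analysis section defines the two rates on a different base. Retention is "the number of patients who complete the follow-up measures at 3 months / the number of enrolled participants". Completion is "the number of complete datasets for each of the outcome measures at 3 months / number of participants enrolled in the study". The same paragraph uses randomized patients as the numerator of the recruitment rate, so it treats enrolled and randomized as separate terms.

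Three other sections show that the two groups need not coincide. Under Participant timeline, consent and enrolment take place before surgery. Under Randomization and masking, "Randomization will be performed immediately following completion of the surgical case". Under Eligibility criteria, patients "found to have a retinal tear during either the pre-operative assessment or intraoperatively will be excluded".

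**The concern.** Feasibility is the primary objective, and this rule is the only stated route from the data to a verdict. Two features leave the verdict open.

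First, the threshold and the rates it is applied to have different denominators. Any patient who consents and enrols but is not randomized is in one denominator and not in the other.

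Second, strict inequalities on both sides leave out the boundary, and at the planned 40 patients the boundary is an attainable count.

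A smaller wording point is that the middle tier, read inclusively, also covers the case where both rates are below 80%, so it overlaps the bottom tier.

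At stake is whether the verdict is fixed before the data are seen, or is chosen afterwards by following one section rather than the other.

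**Working it through.** **The article's own figure.** Sample size gives ±12.4 percentage points for an 80% rate with 40 patients. The Wald half-width is 1.96 × √(0.80 × 0.20 / 40) = 12.4 points, so the figure reproduces with n = 40. With n = 36 (40 less 10% attrition) it would be 13.1. The section does not say whether the 40 are enrolled or randomized, so it does not settle the denominator.

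**Denominator.** Inputs: 40 randomized (planned size, read as randomized) and 40 + k enrolled. The value of k is an assumption, since the article gives none. The table lists every count whose position relative to 80% (above, equal, below) depends on the denominator.

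| Enrolled | Counts that change class | Largest such count, of randomized | Same count, of enrolled |
|---|---|---|---|
| 41 | 32 | 32/40 = 80.0% | 32/41 = 78.0% |
| 42 | 32, 33 | 33/40 = 82.5% | 33/42 = 78.6% |
| 43 | 32 to 34 | 34/40 = 85.0% | 34/43 = 79.1% |
| 44 | 32 to 35 | 35/40 = 87.5% | 35/44 = 79.5% |

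The probability that a single rate changes class is the Binomial(40, p) mass on those counts:

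| Enrolled | p = 0.90 | p = 0.85 |
|---|---|---|
| 41 | 2.6% | 10.9% |
| 42 | 8.4% | 25.8% |
| 43 | 19.1% | 43.2% |
| 44 | 35.5% | 60.1% |

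The value p = 0.90 matches the 10% attrition assumed under Sample size.

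The effect on the verdict depends on both rates. With 42 enrolled:

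- 33 retained and 33 complete is feasible on the randomized base (82.5% for both) and infeasible on the enrolled base (78.6% for both).
- 36 retained and 33 complete is feasible on the randomized base (90.0% and 82.5%) and falls to the middle tier on the enrolled base (85.7% and 78.6%).

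**Boundary.** 32/40 = 80.0% is neither above nor below 80%. The verdict is missing when both rates are at least 80% and at least one equals it. If one rate is exactly 80% and the other is below, the literal wording gives the middle tier. For one rate, P(X = 32) under Binomial(40, p) is 2.6% at p = 0.90, 10.9% at 0.85 and 15.6% at 0.80.

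**Is every tier reachable?** Assume that completers are a subset of those retained, with 40 as the common denominator. There are 41 × 42 / 2 = 861 possible (retained, complete) pairs:

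- top tier, both at least 33: 36
- middle tier, retained at least 32 and complete at most 31: 9 × 32 = 288
- bottom tier, both at most 31: 528
- no verdict: 9

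With 90% retention and an assumed 90% completeness among those retained, the probabilities are about 50% top, 33% middle, 1.5% bottom and 15.4% no verdict.

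**The case against.** The best defence is that the decision rule itself names randomized patients, so a sensible analyst would follow it and treat the enrolled wording as loose usage. A patient with an intraoperative tear is ineligible under the criteria and might be left out of both counts. On that view the conflict has no numerical effect. This is a plausible reading and may be the intended one, so it is not established that such exclusions would be scored as retention failures. But the formulas state the other base, and the same paragraph uses both terms. The intention has to be written down.

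On the boundary, the protocol expects about 10% attrition, and at a true 90% the chance that a given rate is exactly 32/40 is only 2.6%. The higher single-rate figures apply if the true rate is nearer the cut. Exactly 80% also needs a denominator divisible by 5, so with 41 to 44 enrolled it cannot occur on the enrolled base. Both points stand and limit the size of the defect. They do not close the gap at the planned 40.

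It is also fair that this is a pilot whose results will be reviewed before any decision on a main trial, so the rule is not the only safeguard.

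A reader might go further and infer that, because a complete 3-month dataset seems to require 3-month follow-up, the middle tier cannot be reached. The documents do not support that. Adequate retention with low completion leads straight to it, as the count of 288 pairs shows. Nesting removes only the route of low retention with adequate completion, and nesting is itself an inference, because completion is worded per outcome measure. Which measures make up a complete dataset is detail that an article may leave to the full protocol, and it is not pressed here.

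**Conclusion.** The point holds on two counts. The thresholds and the rate definitions use different denominators, and this can move a rate across 80% once any enrolled patient is not randomized. With one such patient and 40 randomized, only 32/40 is affected. With four, every count from 32 to 35 is. How often this would happen cannot be said from the article, because it gives no number for enrolled patients who are not randomized.

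In addition, 32/40 has no verdict when the other rate is at least 80%. The single-rate probabilities of 2.6% to 15.6% assume 40 independent patients with a common rate between 90% and 80%.

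The overlap between the middle and bottom tiers is minor, since the intended reading (exactly one rate below 80%) is clear.

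The rule is otherwise workable, and all three tiers can occur. Because it decides the primary conclusion, the wording should be settled before the data are analysed.

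**What to change.** In Statistical methods and data analysis, use the number randomized as the denominator for both retention and completion, in line with Objectives. Report patients enrolled but not randomized separately, with reasons.

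In Objectives, reword the tiers as follows:

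- feasible: both rates at least 80% of randomized patients;
- feasible with small changes: exactly one rate below 80%;
- infeasible: both rates below 80%.

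With 40 randomized, the cut is then 32 or more against 31 or fewer, and every result falls in one tier. For example, 36/40 retained with 30/40 complete falls in the middle tier.

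Keep completion on the randomized denominator. Defining it among retained patients would bring in a second base again and loosen the rule: 33/40 retained (82.5%) with 27/33 complete (81.8%) would count as feasible although only 27/40 (67.5%) of randomized patients had complete data.

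The cost is a few words in two sections. No new data are needed, and neither the sample size nor the conduct of the trial changes.

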### Trial design

This study will be a single-centered, parallel group randomized controlled pilot trial. Patients will be randomized 1:1 between groups.

## Methods

### Study setting

The study will be conducted at the Hamilton Regional Eye Institute located at St. Joseph’s Hospital in Stoney Creek Ontario. The study protocol is reported in line with the Standard Protocol Items: Recommendations for Interventional Trials (SPIRIT) statement (Table 1) [17]. Ethics approval for this project was granted by the Hamilton Integrated Research Ethics Board (HiREB project ID: 16100). This trial has been registered on clinicaltrials.gov (NCT NCT06000111). This study will adhere to the tenets of the Declaration of Helsinki.

**Table 1 pone.0304566.t001:** SPIRIT checklist.

Section/item	Item No	Description	Page Number
**Administrative information**			
Title	1	Descriptive title identifying the study design, population, interventions, and, if applicable, trial acronym	1
Trial registration	2a	Trial identifier and registry name. If not yet registered, name of intended registry	1
	2b	All items from the World Health Organization Trial Registration Data Set	1
Protocol version	3	Date and version identifier	1
Funding	4	Sources and types of financial, material, and other support	1
Roles and responsibilities	5a	Names, affiliations, and roles of protocol contributors	1, 17
	5b	Name and contact information for the trial sponsor	N/A
	5c	Role of study sponsor and funders, if any, in study design; collection, management, analysis, and interpretation of data; writing of the report; and the decision to submit the report for publication, including whether they will have ultimate authority over any of these activities	N/A
	5d	Composition, roles, and responsibilities of the coordinating centre, steering committee, endpoint adjudication committee, data management team, and other individuals or groups overseeing the trial, if applicable (see Item 21a for data monitoring committee)	N/A
**Introduction**			4
Background and rationale	6a	Description of research question and justification for undertaking the trial, including summary of relevant studies (published and unpublished) examining benefits and harms for each intervention	4
	6b	Explanation for choice of comparators	4,5,9
Objectives	7	Specific objectives or hypotheses	6,7
Trial design	8	Description of trial design including type of trial (eg, parallel group, crossover, factorial, single group), allocation ratio, and framework (eg, superiority, equivalence, noninferiority, exploratory)	7
**Methods: Participants, interventions, and outcomes**			
Study setting	9	Description of study settings (eg, community clinic, academic hospital) and list of countries where data will be collected. Reference to where list of study sites can be obtained	8
Eligibility criteria	10	Inclusion and exclusion criteria for participants. If applicable, eligibility criteria for study centres and individuals who will perform the interventions (eg, surgeons, psychotherapists)	8
Interventions	11a	Interventions for each group with sufficient detail to allow replication, including how and when they will be administered	8,13
	11b	Criteria for discontinuing or modifying allocated interventions for a given trial participant (eg, drug dose change in response to harms, participant request, or improving/worsening disease)	13,14
	11c	Strategies to improve adherence to intervention protocols, and any procedures for monitoring adherence (eg, drug tablet return, laboratory tests)	13,14
	11d	Relevant concomitant care and interventions that are permitted or prohibited during the trial	N/A
Outcomes	12	Primary, secondary, and other outcomes, including the specific measurement variable (eg, systolic blood pressure), analysis metric (eg, change from baseline, final value, time to event), method of aggregation (eg, median, proportion), and time point for each outcome. Explanation of the clinical relevance of chosen efficacy and harm outcomes is strongly recommended	6,7
Participant timeline	13	Time schedule of enrolment, interventions (including any run-ins and washouts), assessments, and visits for participants. A schematic diagram is highly recommended (see Figure)	16,17
Sample size	14	Estimated number of participants needed to achieve study objectives and how it was determined, including clinical and statistical assumptions supporting any sample size calculations	16
Recruitment	15	Strategies for achieving adequate participant enrolment to reach target sample size	17
**Methods: Assignment of interventions (for controlled trials)**			
Allocation:			
Sequence generation	16a	Method of generating the allocation sequence (eg, computer-generated random numbers), and list of any factors for stratification. To reduce predictability of a random sequence, details of any planned restriction (eg, blocking) should be provided in a separate document that is unavailable to those who enrol participants or assign interventions	17,18
Allocation concealment mechanism	16b	Mechanism of implementing the allocation sequence (eg, central telephone; sequentially numbered, opaque, sealed envelopes), describing any steps to conceal the sequence until interventions are assigned	17, 18
Implementation	16c	Who will generate the allocation sequence, who will enrol participants, and who will assign participants to interventions	17,18
Blinding (masking)	17a	Who will be blinded after assignment to interventions (eg, trial participants, care providers, outcome assessors, data analysts), and how	17, 18
	17b	If blinded, circumstances under which unblinding is permissible, and procedure for revealing a participant’s allocated intervention during the trial	N/A
**Methods: Data collection, management, and analysis**			
Data collection methods	18a	Plans for assessment and collection of outcome, baseline, and other trial data, including any related processes to promote data quality (eg, duplicate measurements, training of assessors) and a description of study instruments (eg, questionnaires, laboratory tests) along with their reliability and validity, if known. Reference to where data collection forms can be found, if not in the protocol	15
	18b	Plans to promote participant retention and complete follow-up, including list of any outcome data to be collected for participants who discontinue or deviate from intervention protocols	15
Data management	19	Plans for data entry, coding, security, and storage, including any related processes to promote data quality (eg, double data entry; range checks for data values). Reference to where details of data management procedures can be found, if not in the protocol	15
Statistical methods	20a	Statistical methods for analysing primary and secondary outcomes. Reference to where other details of the statistical analysis plan can be found, if not in the protocol	18, 19
	20b	Methods for any additional analyses (eg, subgroup and adjusted analyses)	N/A
	20c	Definition of analysis population relating to protocol non-adherence (eg, as randomised analysis), and any statistical methods to handle missing data (eg, multiple imputation)	18, 19
**Methods: Monitoring**			
Data monitoring	21a	Composition of data monitoring committee (DMC); summary of its role and reporting structure; statement of whether it is independent from the sponsor and competing interests; and reference to where further details about its charter can be found, if not in the protocol. Alternatively, an explanation of why a DMC is not needed	19
	21b	Description of any interim analyses and stopping guidelines, including who will have access to these interim results and make the final decision to terminate the trial	19
Harms	22	Plans for collecting, assessing, reporting, and managing solicited and spontaneously reported adverse events and other unintended effects of trial interventions or trial conduct	7,19
Auditing	23	Frequency and procedures for auditing trial conduct, if any, and whether the process will be independent from investigators and the sponsor	N/A
**Ethics and dissemination**			
Research ethics approval	24	Plans for seeking research ethics committee/institutional review board (REC/IRB) approval	8
Protocol amendments	25	Plans for communicating important protocol modifications (eg, changes to eligibility criteria, outcomes, analyses) to relevant parties (eg, investigators, REC/IRBs, trial participants, trial registries, journals, regulators)	N/A
Consent or assent	26a	Who will obtain informed consent or assent from potential trial participants or authorised surrogates, and how (see Item 32)	16,17
	26b	Additional consent provisions for collection and use of participant data and biological specimens in ancillary studies, if applicable	N/A
Confidentiality	27	How personal information about potential and enrolled participants will be collected, shared, and maintained in order to protect confidentiality before, during, and after the trial	15,16
Declaration of interests	28	Financial and other competing interests for principal investigators for the overall trial and each study site	21,22
Access to data	29	Statement of who will have access to the final trial dataset, and disclosure of contractual agreements that limit such access for investigators	22
Ancillary and post-trial care	30	Provisions, if any, for ancillary and post-trial care, and for compensation to those who suffer harm from trial participation	N/A
Dissemination policy	31a	Plans for investigators and sponsor to communicate trial results to participants, healthcare professionals, the public, and other relevant groups (eg, via publication, reporting in results databases, or other data sharing arrangements), including any publication restrictions	22
	31b	Authorship eligibility guidelines and any intended use of professional writers	22
	31c	Plans, if any, for granting public access to the full protocol, participant-level dataset, and statistical code	N/A
**Appendices**			
Informed consent materials	32	Model consent form and other related documentation given to participants and authorised surrogates	N/A
Biological specimens	33	Plans for collection, laboratory evaluation, and storage of biological specimens for genetic or molecular analysis in the current trial and for future use in ancillary studies, if applicable	N/A

### Eligibility criteria

All consecutive treatment naïve patients with an idiopathic FTMH with a symptom duration of less than 6 months who agree to participate will be included in this investigation. Patients with macular hole minimum diameter >1000 μm, a history of high myopia (> -6), traumatic macular hole, amblyopia, retinal vein occlusion, inflammatory eye diseases, or who were found to have a retinal tear during either the pre-operative assessment or intraoperatively will be excluded.

